#### Study population

All women expecting to deliver vaginally at the participating hospitals will be potentially eligible. Women will be approached primarily during antenatal care and early labour for consent for participation except under the following circumstances;

1. Advanced first stage of labour (> 6 cm cervical dilatation)

2. Women who are too distressed to give consent regardless of cervical dilatation or phase of labour. Such evaluation will be made by the clinician in charge of the care of the woman.

3. Minors without a guardian

4. Planned caesarean section

5. If the birth is considered an abortion according to local limits

6. Women with twins or higher order multiple gestations

7. Women who are not capable of giving consent due to other health problems such as obstetric emergencies (e.g. eclampsia) or mental disorder.

Women receive AMTSL regardless of whether they are at high or low-risk for haemorrhage. Therefore all women will be eligible for participation according to the exceptions mentioned above.

## Methods

### Generation of allocation sequence

The random allocation sequence will be generated centrally at WHO Headquarters using computer generated random numbers. Randomization will be to two groups and stratified by country. Blocking with randomly varying groups of 6–8 will be used to restrict randomization within the strata.

### Random allocation technique and allocation concealment

Allocation of the random generated sequence will be by consecutively numbered envelopes. Allocation concealment will be achieved by using sealed opaque envelopes. Allocation will take place during second stage when vaginal delivery is imminent. Once the envelope is opened the name of the woman will be entered on the log file with the envelope number and that woman is enrolled in the trial.

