### Study design

This will be a hospital-based, multicentre, individually randomized non-inferiority controlled trial.

Each woman will be randomized to receive either the full (AMTSL) package or the simplified package. The blinding of the intervention will not be possible because the comparison includes a manual procedure.

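### The envelope is opened before the woman is recorded against it, so in this unmasked trial an allocation can be seen before it is tied to a particular woman

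*Protocol article*

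**What the plan says.** The section on random allocation technique and allocation concealment in the protocol article gives the whole procedure. The order of use is fixed first: "Allocation of the random generated sequence will be by consecutively numbered envelopes." The device that hides the arm comes next: "Allocation concealment will be achieved by using sealed opaque envelopes." The article then places the step late in labour: "Allocation will take place during second stage when vaginal delivery is imminent." The sentence at issue closes the section: "Once the envelope is opened the name of the woman will be entered on the log file with the envelope number". Its final clause sets the point of enrolment: "and that woman is enrolled in the trial".

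Three other sections bear on it:

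- Study design: "The blinding of the intervention will not be possible because the comparison includes a manual procedure."
- Generation of allocation sequence: "Blocking with randomly varying groups of 6–8 will be used to restrict randomization within the strata."
- Study population: "Women will be approached primarily during antenatal care and early labour for consent for participation."

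The analysis plan makes intention-to-treat the main analysis.

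**The concern.** As written, opening comes first, and the entry of the name and enrolment follow. Between opening and entry, an unmasked member of staff knows the arm, and no record yet shows whom the envelope was opened for. Two things are then possible. The opened envelope can be used for a different consented woman in second stage, or the first woman can be managed outside the trial and never logged.

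The motive is plausible. The article admits women at high as well as low risk of haemorrhage, and it calls the full package the gold standard. A clinician who is uneasy about omitting cord traction in a high-risk woman has a reason to keep her out of the simplified arm. That would lower the observed event rate in the simplified arm and push the result towards non-inferiority. Intention-to-treat analysis cannot repair this, because a woman who was never logged is not in the analysis set.

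**Working it through.** **The text.** The question for each stated safeguard is whether it ties a named woman to an envelope number before opening.

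| Safeguard | What it does | Ties a woman to an envelope before opening? |
|---|---|---|
| Sealed, opaque envelopes | Hide the arm until opening | No |
| Consecutive numbering | Exposes a missing or skipped number | No; a reassigned envelope is still used and logged in order |
| Consent sought earlier | Fixes who may be enrolled | No; it links no woman to a number |
| Allocation when delivery is imminent | Leaves little time to rearrange | No |
| Varying block size | Makes the next allocation harder to guess | No; it acts before opening |

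**The plan's own figures.** Table 1, row 1 uses 1.5% in both arms, a margin of 0.45 points, one-sided 2.5% and 80% power:

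n per arm = (1.960 + 0.842)² × 2 × 0.015 × 0.985 / 0.0045² ≈ 11,454, so N = 22,908, as stated.

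Power is 74.5% at 20,000 and 83.3% at 25,000 (stated: 75% and 83%). For a margin of 0.50 points the same formula gives 18,556 (stated: 18,555). The order of logging and opening enters none of these figures.

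**Illustration of the stakes.** From the article: N = 25,000, full-package rate 1.5%, margin 0.45 points. Equal allocation (12,500 per arm) is assumed. The true simplified-arm rate is set at the margin, 1.5 + 0.45 = 1.95%, where the chance of wrongly declaring non-inferiority should be 2.5%. The standard error of the difference is

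√(0.015 × 0.985 / 12,500 + 0.0195 × 0.9805 / 12,500) = 0.165 points.

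(The value 0.154 applies only when both arms are at 1.5%.)

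Suppose a fraction f of simplified-arm women, each with risk r, is removed after the envelope is seen. Both f and r are assumptions. Then

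- observed rate = (1.95% − f × r) / (1 − f)
- chance of declaring non-inferiority = Φ[(0.45 − observed difference) / SE − 1.96], with the SE recalculated at the observed rates.

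| f | r | Women removed | Observed rate | Shift (points) | False non-inferiority |
|---|---|---|---|---|---|
| 0 | – | 0 | 1.950% | 0 | 2.5% |
| 0.5% | 10% | about 63 | 1.910% | 0.04 | 4.3% |
| 1% | 5% | 125 | 1.919% | 0.03 | 3.8% |
| 1% | 10% | 125 | 1.869% | 0.08 | 7.2% |
| 2% | 10% | 250 | 1.786% | 0.16 | 17% |

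For the last row: (1.95 − 0.20)/0.98 = 1.786. The shift of 0.164 is about one standard error, or 36% of the margin (0.164/0.45).

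The table covers women who leave the trial. Women moved into the full arm do more harm, because both rates change. Counted in events, losing 5% of would-be simplified-arm events (about 12 women) gives 8.5%. Moving the same women to the full arm gives rates of 1.853% and 1.598%, a difference of 0.255 points, and a false non-inferiority risk of 21.9%. With a margin of 0.50 points these become 8.7% and 22.5%.

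**The case against.** The strongest reply is that the sentence concerns one identified woman for whom the envelope is opened, so opening is itself the point of enrolment. The analysis plan fits this reading, since it treats withdrawal of consent after random allocation as a deviation. That would be a sound intention-to-treat rule, and the reading is fair. What remains is that no record made before opening enforces it.

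A second reply is that names on envelopes, time stamps and reconciliation belong in the manual of operations, which is not shown. That would answer a complaint that the article is silent. But the article states an order, and the order it states is the weaker one. The manual may add a prior step, but nothing visible supplies it.

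Third, other safeguards exist. The log ties name to number, so an opened envelope with no entry leaves a gap. Total births are collected, staff are trained and monitored, the data monitoring committee looks at protocol deviations, and actual third-stage management is recorded for every woman. These reduce the risk and make omission detectable if envelopes are accounted for. They do not reveal an envelope used for a different woman.

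Fourth, the diversion rates are assumed. This stands in full. The 2% row needs 250 women in the simplified arm, each at about five times the average risk, to be identified and diverted. The direction of bias also depends on assumed staff preferences.

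Two stronger readings are tempting. A reader might infer that this is the only point where selection can enter. It is not: clinical judgement about who can consent, and recruitment that is not round the clock, also select women, though before allocation. A reader might also add that small blocks make the next allocation guessable. Correct guesses of about 67%, against 50% by chance, require 1:1 allocation and someone who sees every earlier allocation in the country's sequence. That is an upper bound, and recording before opening would not change it.

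**Conclusion.** The point holds as a procedural weakness in stated text. The envelope is opened before the woman is recorded against it, and the article describes nothing that commits her to it beforehand. Reassignment to another consented woman is the case the stated safeguards would miss; omission is easier to detect. The documents do not support a claim that subversion is expected or that the result would be biased. Under assumed selective removal of 0.5% to 2% of simplified-arm women at 5% to 10% risk, the false non-inferiority risk moves from 2.5% to between about 4% and 17%, and the error favours the trial's hypothesis. Few events drive the conclusion (1.95% of 12,500 is about 244), so a small number of selectively handled women could matter. It is worth changing mainly because the change is so cheap.

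**What to change.** Reverse the order in the allocation section and in the manual of operations:

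1. Before opening, write the woman's identifier, the date and the time in the log against the next envelope number, and on the sealed envelope itself.
2. Define that entry as randomisation, so that she stays in the intention-to-treat set whatever happens next.
3. Have the trial centre reconcile envelopes, log entries and times, and report any envelope missing or opened out of order.

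The cost is a short change of wording, a printed line on the envelope, a few seconds per woman and some reconciliation work at the centre. It needs no extra staff at delivery. The margin, power and sample size stay as they are.

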### Rationale for the non-inferiority hypothesis and for sample size estimation

The objective of this trial is to show 'non-inferiority' of the simplified package' compared to the full AMTSL package. As such, while superiority would be an added bonus it is not expected and is probably not plausible since the experimental intervention has fewer interventions.

In the conventional superiority trial, the aim is to determine whether one intervention is superior to another, for example, whether uterotonic is superior to nothing. By contrast, in a non-inferiority trial, the aim is to determine whether an alternative intervention with certain advantages is similar to a gold standard. The full AMTSL package represents the gold standard management strategy for reducing blood loss in the third stage of labour. In order to evaluate the effectiveness of a simplified package with fewer components that package has to be compared to the full package to see whether t is "non-inferior" to the gold standard [17].

Because proof of exact equality is impossible, a pre-stated margin of non-inferiority (Δ) for the difference in effectiveness has to be defined. The choice of the non-inferiority margin can be made using clinical assessment, which is to a certain extent arbitrary, and needs consensus among different stakeholders. A technique which has been proposed [17] to establish the non-inferiority margin is to look at the effect of the gold standard, in this case the full AMTSL, compared with placebo in historical (past) trials, in this case the expectant management. A reasonable criterion is to preserve 80% of the benefit of the full AMTSL package (considered as 100%) over expectant management (considered as 0%). Preserving a higher percentage (say 90%) will push the sample size calculations very high while a smaller percentage (say 50%) may not be considered acceptable.

Estimates of blood loss ≥ 1000 ml (severe PPH – sPPH) with active and passive management were taken from the literature. In addition, unpublished data from several ongoing WHO studies where postpartum blood loss is measured were obtained. Based on those data, a 1.5% risk of blood loss of 1000 ml with full active management was considered realistic and appropriate.

The expectant management sPPH rate was more difficult to estimate because the data was only available from earlier published trials and blood loss estimation methods and the actual expectant management method differed between trials. Values between 3.0 to 4.0% are considered realistic and used for sample size estimations.

Table 1 includes different scenarios for the calculation of sample size, obtained by varying the sPPH rate with expectant management (3.0 to 4.0%) and varying the % retained effect (70% to 80%), assuming a fixed 1.5% sPPH rate for the full AMTSL package. These different scenarios result in different choices of the margin of non-inferiority **Δ**. The total sample size required for a non-inferiority test at the 2.5% level using a two-sided 95% confidence interval and a power of 80% is shown, as well as the power obtained for fixed sample sizes of 20,000 and 25,000.

**Table 1 T1:** Sample size scenarios

Blood loss ≥ 1000 ml with full amtsl	Blood loss ≥ 1000 ml with Expectant	Estimated impact of Full AMTSL	Proportion (of full AMTSL effect) retained by the simplified package	Δ (Difference to exclude to claim equivalence)	Total N for 80% Power	Power with total N = 20,000	Power with total N = 25,000
1.5	3.0	1.5	0.7	0.45	22,908	75%	83%

1.5	3.5	2.0	0.75	0.50	18,555	83%	90%

1.5	4.0	2.5	0.8	0.50	18,555	83%	90%

A trial of 22,908 women will have 80% power to show non-inferiority of the simplified package within 0.45% of the full AMTSL package sPPH rate (i.e. less than 1.95% sPPH rate), with a level of significance of 2.5% (Table 1, row 1). The estimates from the centres that have expressed interest in participating in the trial indicate that approximately 20,000–25,000 women can be recruited in a 12 months recruitment period. These centres have collaborated with WHO before and have experience in third stage trials.

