## Background

The third stage of labour refers to the period between birth of the baby and complete expulsion of the placenta. Some degree of blood loss occurs after the birth of the baby due to separation of the placenta. This period is a risky period because uterus may not contract well after birth and heavy blood loss can endanger the life of the mother.

The third stage of labour is managed differently around the world. Over the years two management packages, known as 'active management' and 'expectant management' emerged. The primary aim of active management is to reduce postpartum blood loss as a preventive intervention. In active management (AMTSL) a number of interventions are applied in combination while the expectant management represents a more hands-off style with those interventions used in AMTSL withheld. AMTSL has been defined in various ways and current international definition comprises three components: administration of an uterotonic soon after delivery of the baby; controlled cord traction; and uterine massage after delivery of the placenta [1]. Active management of the third stage of labour (AMTSL) reduces the occurrence of severe postpartum haemorrhage by approximately 60–70% [2].

In previous active versus expectant trials the cord was clamped as soon as possible usually within one minute. However, trials of cord clamping timing have shown beneficial effects on newborn haematological indices leading to the recommendation to clamp the cord at around 3 minutes although the effects on the mother are unknown [3].

The WHO PPH Prevention Guidelines published in 2007 recommended AMTSL defined as the use of oxytocin 10 IU IM/IV after birth, cord clamping at around 3 minutes when the uterus contracts and controlled cord traction. There were no recommendations related to the use of uterine massage in this guideline.

Unfortunately, the relative contribution of the components of AMTSL to the overall reduction in blood loss is not clearly known. Understanding the contribution of the components of AMTSL to the overall effect in reducing the incidence of haemorrhage could have major programmatic significance since some components require training while others require an efficient drug procurement and utilization system [4]. At the same time the probability of interaction between AMTSL components should be kept in mind.

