### Objective

The primary objective is to determine whether the simplified package of oxytocin 10 IU IM/IV, without CCT, is not less effective than the full AMTSL package with regard to reducing blood loss ≥ 1000 ml in the third stage of labour. The hypothesis will be that of non-inferiority within a margin of 0.45 to 0.50%. If this hypothesis is demonstrated, the simplified package without CCT could be adopted, with the advantage of not requiring training to acquire the manual skill to perform this task.

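### The 0.45 to 0.50 point margin secures the stated 80% of the AMTSL benefit only if the expectant rate is at least 3.75% to 4.0%; the row cited for the sample size secures 70%

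*Protocol article*

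**What the plan says.** All references are to the protocol article.

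- **Rationale for the non-inferiority hypothesis and for sample size estimation.** The margin is built from the benefit of full AMTSL over expectant management in past trials. The criterion is: "A reasonable criterion is to preserve 80% of the benefit of the full AMTSL package". The section sets aside 90% because of its sample size, and adds that "a smaller percentage (say 50%) may not be considered acceptable".
- **Same section, inputs.** For the control arm, "a 1.5% risk of blood loss of 1000 ml with full active management was considered realistic and appropriate". For expectant management, "Values between 3.0 to 4.0% are considered realistic and used for sample size estimations".
- **Same section, Table 1.** The scenarios come from changing the expectant rate and from "varying the % retained effect (70% to 80" per cent). Expectant rates of 3.0%, 3.5% and 4.0% are paired with retained shares of 0.70, 0.75 and 0.80, giving margins of 0.45, 0.50 and 0.50 points.
- **Same section, text after Table 1.** The sample-size statement rests on row 1: "A trial of 22,908 women will have 80% power to show non-inferiority of the simplified package within 0.45" percentage points.
- **Objective.** "The hypothesis will be that of non-inferiority within a margin of 0.45 to 0.50" per cent.
- **Background.** AMTSL "reduces the occurrence of severe postpartum haemorrhage by approximately 60–70" per cent.

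**The concern.** The rationale argues for one retention level, 80%, against two alternatives, 90% and 50%. It gives no argument for 70% or 75%. Yet 80% appears in Table 1 only at the top of the expectant range. As the assumed expectant rate falls, the retained share falls with it, so the margin stays near 0.45 to 0.50 and the sample size stays within the 20,000 to 25,000 women whom the centres can recruit.

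Two things are at stake. A reader of the rationale may take the trial as designed to protect 80% of the benefit, when over most of the assumed range its margin protects less. And the Analysis plan judges the result against a pre-stated margin, while the Objective gives an interval. An upper confidence limit of, say, 0.47 points would be non-inferior against 0.50 and not against 0.45.

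**Working it through.** **Inputs.** Control risk 1.5%; expectant rate 3.0% to 4.0%; test level 2.5% with a two-sided 95% interval; power 80% (all from the rationale section). Two assumptions: 1:1 allocation and a true difference of zero. Both are supported by the match in step 1.

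**Step 1: reproduce Table 1.** With p = 0.015 and margin Δ,

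n per arm = (1.96 + 0.8416)² × 2 × p(1 − p) / Δ².

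- Δ = 0.0045: 7.849 × 0.02955 / 0.00002025, rounded up to 11,454 per arm, total 22,908 (stated 22,908).
- Δ = 0.0050: 9,278 per arm, total 18,556 (stated 18,555, a rounding difference).

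Power = Φ(Δ/SE − 1.96), with SE = √(2p(1 − p)/(N/2)). At N = 25,000, SE is 0.1537 points. Power is 83.3% for 0.45 and 90.2% for 0.50 (stated 83% and 90%). At N = 20,000 it is 74.5% and 82.9% (stated 75% and 83%). Table 1 is correct.

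**Step 2: share of benefit retained.** Retained = 1 − Δ/(expectant − 1.5), in percentage points.

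| Expectant rate | Benefit | Retained, Δ = 0.45 | Retained, Δ = 0.50 |
|---|---|---|---|
| 3.0% | 1.5 | 70% | 66.7% |
| 3.5% | 2.0 | 77.5% | 75% |
| 4.0% | 2.5 | 82% | 80% |

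**Step 3: where 80% is reached.** This needs Δ ≤ 0.2 × (expectant − 1.5). For 0.45 the expectant rate must be at least 1.5 + 0.45/0.2 = 3.75%. For 0.50 it must be at least 1.5 + 0.50/0.2 = 4.0%. So 0.45 falls short over three quarters of the 3.0% to 4.0% range, and 0.50 meets 80% only at its upper end. At 3.0%, 0.50 retains 66.7%, which is below every level in Table 1.

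**Step 4: what holding 80% would require.**

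| Expectant rate | Δ for 80% | Total N, 80% power | Power at 22,908 | Power at 25,000 |
|---|---|---|---|---|
| 3.0% | 0.30 | 51,542 | 46% | 50% |
| 3.5% | 0.40 | 28,992 | 70% | 74% |
| 4.0% | 0.50 | 18,556 | 88% | 90% |

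**Step 5: the cited relative benefit.** At a 1.5% control risk, a 60% reduction implies an expectant rate of 1.5/0.4 = 3.75%, and a 70% reduction implies 1.5/0.3 = 5.0%. Then 0.45 retains 1 − 0.45/2.25 = 80% and 1 − 0.45/3.5 = 87%; 0.50 retains 78% and 86%. Row 1's 3.0% corresponds to a 50% reduction, which is more cautious than the cited range.

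**The case against.** The strongest defence is that nothing is hidden. The text says that the retained share was varied, Table 1 prints it in its own column, and 80% is offered as a reasonable criterion, not a binding rule. The same section calls the clinical choice of margin partly arbitrary. All of that stands. It answers a charge of concealment or miscalculation, but it does not supply a reason for 70% or 75%.

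Some stronger readings are tempting, and the document does not support them.

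- *The margin fails the 80% criterion outright.* An absolute margin has no single retained share. At 4.0%, which the protocol regards as realistic, 0.45 retains 82%. Under the 60–70% reduction cited in the Background, it retains 80% to 87%.
- *A positive trial could not support 80%.* It could. An upper limit below 0.30 points shows 80% retention even at an expectant rate of 3.0%. At 25,000 women and 1.5% risk the 95% half-width is 1.96 × 0.1537 = 0.30 points, so with no true difference this would happen about half the time.
- *The conclusion attached to a positive result is false.* The Analysis plan promises only non-inferiority relative to the margin. It does not promise 80% retention.
- *A lower control risk would necessarily erode the criterion.* As an illustration, at a control risk of 1.0%, 0.45 retains 1 − 0.45/1.5 = 70% under a 60% reduction and 1 − 0.45/2.33 = 81% under a 70% reduction. The answer depends on an expectant rate that the trial does not observe, and the protocol states its 1.5% assumption. This merits at most a supportive calculation.

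**Conclusion.** The point holds as an inconsistency between the named criterion and the margin used. It is not an arithmetic error. With a 1.5% control risk, the 0.45 to 0.50 margin guarantees 80% of the benefit only if the expectant rate is at least 3.75% (for 0.45) or 4.0% (for 0.50). Under row 1, the only row cited for the sample size, the guarantee is 70%; with 0.50 at the same expectant rate it would be 67%. The 70% to 80% range is disclosed but not justified, and the Objective leaves the decision threshold as a range. The retained shares rest on the protocol's own rates; the power and sample-size figures also assume 1:1 allocation and no true difference.

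**What to change.** 1. In the Objective, state a single margin of 0.45 percentage points and drop 0.50.
2. In the rationale section, replace the general 80% criterion with the property that the margin has: *With a 1.5% control risk, Δ = 0.45 preserves 70%, 77.5% and 82% of the benefit at expectant rates of 3.0%, 3.5% and 4.0%, and 80% or more only from 3.75%.*
3. Optionally, in the final report, show the retained share at the observed control risk under the cited 60–70% relative reduction, labelled as supportive because the expectant rate is assumed. With control risk c (in %) and relative reduction r, it is 1 − Δ(1 − r)/(c × r).

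**Cost.** Wording and one optional calculation; no additional women, since 25,000 give 83% power at 0.45. The sponsor gives up the more favourable 80% statement and the 90% power that Table 1 shows for 0.50.
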